Usability will be evaluated using the Malay version of the Mobile Health App Usability Questionnaire (M-MAUQ) [21]; its conceptual framework and item pool are grounded in the original English MAUQ development and validation by Zhou et al. [22]. The 18-item instrument includes three domains, namely, ease of use (5 items), interface satisfaction (7 items), and usefulness (6 items), rated on a 7-point Likert scale (1 (strongly disagree) to 7 (strongly agree)). Acceptable usability is defined beforehand as a mean item score above 4.0 (i.e., above the neutral midpoint), which corresponds to a total score of 72 or higher out of 126 (18×4). This threshold indicates a clear tendency toward positive usability on a 7-point scale and is commonly used for MAUQ-based app evaluations when no specific clinical cut-points are available. For better understanding, we will also report categories at the domain level: minimal acceptable (>4.0 to <5.0), good (≥5.0 to <6.0), and excellent (≥6.0). Phase 1b will use a cross-sectional, post-use design with an independent sample of approximately 100 MMH workers. Participants will receive a brief orientation and a guided first use of the ARPE app and then complete the M-MAUQ immediately afterward in the same session. Regarding feedback, we will calculate mean scores for each domain and item; any item with a mean score of 4.0 or less, a corrected item-total correlation below 0.30, or recurring free-text concerns will be flagged for revision. Results will be compiled into an action log (UI issues, content clarity, navigation), prioritized by severity and frequency, and addressed quickly before starting the Phase 2 quasi-experimental study. Reliability (Cronbach's α; optional test-retest ICC in a subsample) will be reported according to the thresholds specified in the Assessment Tool Development and Validation subsection.

Phase 2: evaluation of the AR ergonomic training module's effectiveness

This Phase 2 evaluation employs a two-arm, parallel-group, quasi-experimental design among warehouse MMH workers. To minimize cross-group contamination at the worksite, allocation is non-randomized at the site level to (i) ARPE training (intervention) or (ii) standard guideline-based training (control) in approximately a 1:1 ratio. We will report baseline comparability between groups in terms of demographics, job tenure, department/shift, prior ergonomic training, and baseline outcomes. Any imbalances will be addressed analytically.

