## Results

Planned outcomes and data analysis

Since this is a protocol, no results are available yet. The primary outcome is ergonomic knowledge, while secondary outcomes include self-prevention behaviors and self-evaluation, measured at baseline (T0), post-training (T1), and six weeks later (T2). Analyses will follow intention-to-treat principles using repeated-measures mixed models (fixed effects: group, time, group×time), with site effects and adjustments for baseline scores and prespecified covariates (e.g., age, tenure, department/shift, prior training). Two-sided α=0.05; results will be reported as adjusted mean differences with 95% CI. Sensitivity analyses will incorporate site-clustered standard errors (SEs), a random intercept for the site if applicable, and inverse-probability-of-treatment weighting. Outcome assessors and the statistician will remain blinded to group allocation. 

Protocol Status and Timeline

Recruitment and baseline assessments are ongoing; follow-up continues through November 2025, after which data will be cleaned and analyzed. No interim results are available.

Interpretation of Change

A structured outcome framework was created to assess the effectiveness of the ARPE training module. The assessments are divided into three domains: ergonomic knowledge (the primary outcome), self-prevention behaviors (secondary outcome 1), and self-evaluation skills (secondary outcome 2). Each domain is evaluated at three key timepoints: baseline (t_0_, before the intervention), week 1 (t1, after the intervention to assess knowledge), and week 6 (t2, follow-up post-intervention). The tools used are adapted from Diego-Mas et al. [14]. All scales are scored so that higher scores reflect better outcomes. The primary endpoint is the change in ergonomic knowledge from baseline to immediate post-training (T0→T1). ARPE will be considered superior if the adjusted group-time effect (ARPE-control) is positive with a 95% CI that does not include 0 (two-sided α=0.05); persistence will be evaluated at T2. For secondary domains (self-prevention, self-evaluation), adjusted group×time effects at T1 and T2 will be regarded as improvements when the 95% CI excludes 0; these analyses are exploratory and supportive.

Baseline Characteristics

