Baseline characteristics are summarized in Table 1: continuous variables are presented as mean (SD) or median (IQR), while categorical variables are shown as n. These include age, sex, ethnicity, education, job category, employment duration, shift work, MMH process details, and prior ergonomic training. To evaluate comparability between groups at t_0_, SMDs will be used instead of significance tests. Thresholds for SMD are as follows: <0.10 (negligible), 0.10-0.20 (small), and >0.20 (substantial imbalance). Variables with SMD >0.20, along with prespecified covariates such as age, tenure, department/shift, and prior training, will be adjusted for in the repeated-measures mixed models. These models will incorporate site effects and cluster-robust SEs, as detailed in the Statistical Analysis section. If baseline p-values are reported, they are purely descriptive and not used to determine equivalence.

Primary Outcome: Ergonomic Knowledge

Repeated measures (t_^0^_, t_1_, t_2_) will be analyzed using generalized estimating equations (GEE). The model includes group (ARPE vs. control), time, group×time interaction, site (fixed effect), and prespecified covariates (e.g., age, department/shift, prior training). The primary comparison is the adjusted ARPE-control difference at t_1_, obtained from the group×time term (with baseline accounted for by including t0 in the repeated-measures model); durability will be evaluated at t_2_. Results will be reported as marginal adjusted mean differences (95% CI; two-sided α=0.05) and SMDs. Within-group changes across (t_0_, t_1_, t_2_) will be derived from model-based marginal contrasts with 95% CI. Missing data will be managed under missing completely at random (MCAR)/missing at random (MAR) assumptions using GEE with robust SEs, with sensitivity analyses employing inverse-probability-weighted GEE and multiple imputation.

Secondary Outcome 1: Self-Prevention 

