Analyses will be conducted using IBM SPSS Statistics for Windows, Version 29.0 (IBM Corp., Armonk, New York, United States). After cleaning and verifying the data, descriptive statistics will summarize continuous variables as mean (SD) or median (IQR) and categorical variables as n (%). Baseline comparability will be assessed with SMDs (<0.10 negligible; 0.10-0.20 small; >0.20 meaningful); any baseline p-values are for descriptive purposes only.

Effectiveness analyses will use GEE with an identity link and Gaussian family, clustering on participants with robust (sandwich) SEs and an exchangeable working correlation; QIC will compare the exchangeable structure with AR(1)/unstructured structures. Models will include group (ARPE vs. control), timepoints (t_0_, t_1_, t_2_), group×time interactions, site (fixed effect), and prespecified covariates (age, job tenure, department/shift, prior ergonomic training). The primary comparison is the adjusted ARPE-control difference at t_1 _for ergonomic knowledge (0-100%); durability will be assessed at t_2_. Within-group changes (t_1_-t_0_, t_2_-t_0_) will be derived from model-based marginal contrasts and presented descriptively. Results will be shown as marginal adjusted mean differences with 95% CI (two-sided α=0.05) and SMDs. All analyses will follow intention-to-treat principles. Missing repeated measures will be addressed under MCAR/MAR assumptions via GEE with robust SEs; inverse-probability-weighted GEE and multiple imputation sensitivity analyses will also be reported. For multiple secondary domains and timepoints, multiplicity will be controlled using the Benjamini-Hochberg FDR (q=0.05) method, with both raw and FDR-adjusted p-values presented.

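### Covariates entered without time interactions leave the deciding group×time contrast unadjusted for measured confounding of change

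*Protocol article*

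**What the plan says.** The protocol article, Results, Primary Outcome: Ergonomic Knowledge, treats all three visits as responses and lists the terms as group, time, "group×time interaction, site (fixed effect), and prespecified covariates (e.g., age, department/shift, prior training". The primary comparison is "obtained from the group×time term (with baseline accounted for by including t0 in the repeated-measures model". Data Analysis repeats the structure with the fuller list "site (fixed effect), and prespecified covariates (age, job tenure, department/shift, prior ergonomic training" and specifies an identity link, Gaussian family and exchangeable working correlation, with QIC used to compare alternatives. The two secondary outcomes use the same set of terms. Nowhere is a covariate interacted with time.

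Interpretation of Change sets the decision rule: "ARPE will be considered superior if the adjusted group-time effect (ARPE-control) is positive with a 95% CI that does not include 0".

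The covariates are there to deal with non-random allocation of one warehouse per arm. The Phase 2 overview says "Any imbalances will be addressed analytically". Baseline Characteristics adds that variables with SMD above 0.20, together with the prespecified ones, "will be adjusted for in the repeated-measures mixed models".

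The opening paragraph of Results describes a different primary analysis: a mixed model that also adjusts for baseline score. It lists inverse-probability-of-treatment weighting (IPTW) as a sensitivity analysis.

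**The concern.** The group×time coefficient compares the arms on within-person change. Age, tenure, department/shift and prior training are baseline characteristics. Entered once, each moves a worker's expected score by the same amount at t0, t1 and t2 and therefore cancels from the change.

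The contrast already deals with workers who start higher or lower for stable reasons. What it leaves open is workers who gain differently: for example, younger workers or those with earlier training may learn more from any session. If the warehouses differ on such characteristics, the difference in gain is attributed to ARPE. The listed covariates appear to guard against this, and the result will be reported as adjusted, but under the stated model they do not act on it. The SMD rule fails in the same way: an imbalance would be found and its covariate added, and the primary estimate would not respond.

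**Working it through.** The plan gives no figure on this point to reproduce. Inputs from the protocol are 39 workers per arm and 40% anticipated attrition (Sample Size), three visits, and the model terms above. Covariate imbalances and effects on gain are not in the documents and are assumed below.

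**1. Algebra, complete data.** Write the model as E(Y_it) = μ(g,t) + x_i′γ, where g is the arm and x_i holds the time-invariant covariates. Site coincides with group, so the site term adds nothing (design matrix rank 6 of 7 columns). For any working covariance V common to all participants, the estimating equations for arm g are

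V⁻¹ Σ_i [Y_i − μ(g) − 1·x_i′γ] = 0, so μ̂(g,t) = Ȳ(g,t) − x̄_g′γ̂.

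The group×time estimate at t1 (A = ARPE, C = control) is then

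[μ̂(A,1) − μ̂(A,0)] − [μ̂(C,1) − μ̂(C,0)] = [Ȳ(A,1) − Ȳ(A,0)] − [Ȳ(C,1) − Ȳ(C,0)].

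The term x̄_g′γ̂ is the same at both visits and cancels. Nothing depends on V, so QIC selection does not matter. A baseline-score main effect cancels too while t0 stays in the response.

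**2. Numerical check of the identity.** On complete simulated data the t1 and t2 estimates with and without a covariate agreed to about 1e-14 under independence, exchangeable, AR(1) and unstructured working covariance. In the GEE simulation of step 4 the robust SE was also identical (3.07 and 3.07).

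**3. Size of the bias.** If the arms differ by δ SD on a covariate and gain changes by β points per SD, the bias in the contrast is δ × β:

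| δ (SD) | β (points of gain per SD) | Bias (points) |
|---|---|---|
| 0.20 (the plan's SMD threshold) | 0 | 0 |
| 0.20 | 8 | 1.6 |
| 0.80 | 8 | 6.4 |

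**4. Simulation.** Assumptions: true effect 0, 39 per arm, δ = 0.8, β = 8, residual and random-intercept SD 8, 60 replicates. The second column has about 40% covariate-dependent dropout. Mean group×time estimate at t1 (for the ANCOVA-type row, the group difference at t1):

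| Model | Complete data | About 40% dropout |
|---|---|---|
| No covariates | 6.72 | 6.62 |
| Covariates as listed | 6.72 | 6.76 |
| Covariate×time added | 0.35 | 0.58 |
| ANCOVA-type on t1/t2 | 0.30 | 0.48 |
| IPTW | 0.84 | 1.52 |

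Monte Carlo error is about 3.07/√60 = 0.40, so 6.72 is consistent with the 6.4 of step 3. Under dropout, adding the covariates as listed moved individual estimates by 0.47 points on average and 1.41 at most, without removing the bias.

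**5. A second scenario.** The arms were assumed to differ by 5 years in age and 30 percentage points in prior training, both affecting gain, with true effect 0 and 400 replicates. The mean estimate was 3.83 as specified and −0.10 with covariate×time terms.

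**The case against.** The best reply is that the text admits other readings. No sentence says the covariates are main effects only, and the article condenses a fuller plan. The baseline-score adjustment in the opening paragraph of Results could mean a model of t1 and t2 on baseline, in which covariate main effects do adjust the contrast. Data Analysis speaks of an adjusted difference at t1; read as group plus group×time, that quantity responds to main effects.

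These points show an inconsistency that needs resolving, but they do not rescue the stated model. The primary-outcome section keeps t0 as a response and says the comparison comes from the group×time term, and the endpoint is defined as change. The t1-difference reading would not give the right answer either. In the step 4 simulation the group coefficient moved from 5.00 to −4.36, so the t1 difference moved from 5.00 + 6.72 = 11.72 to −4.36 + 6.72 = 2.36, with a true value of 0.

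Three stronger statements that a reader might infer are not supported:
- That the covariates can never move the estimate. This is exact only with complete data, and the plan expects 40% attrition.
- That the primary analysis has no other worker-level protection. Using change removes every stable level difference between workers, measured or not.
- That the trial's result will be biased by a known amount. The sizes above are assumed. Eligibility also excludes workers trained in the past six months, which limits one source of imbalance.

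It is also fair that IPTW is prespecified and acts on measured confounding of change, and that the Discussion concedes residual confounding. IPTW is a sensitivity analysis, however, and the superiority rule does not refer to it. The weighted GEE named in the outcome sections is there for missing data.

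**Conclusion.** The point holds for the model as written. With complete data the listed and SMD-triggered covariates have no effect on the group×time estimate. Under the anticipated attrition the effect is small and does not remove the bias. The effect on which superiority is declared is thus described as adjusted but is not adjusted for measured differences in gain between the two warehouses' workers. The same applies to the group×time tests of both secondary outcomes.

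The cancellation follows from the stated terms and needs no assumption about the data beyond completeness. The size of the bias does rest on assumptions: it is imbalance times effect on gain, from 0 when the covariates do not affect gain to about 6.4 points at the largest values tried. Because the deciding contrast of a non-randomised comparison is affected, this should be settled before analysis; the protocol reports follow-up still running and no results available.

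**What to change.** Prespecify covariate×time terms for age, tenure, department/shift and prior training, and for any covariate the SMD rule brings in, in the primary and both secondary models. The alternative is an ANCOVA-type model with t1 and t2 as responses and baseline score and covariates as predictors. The two can differ when arms differ at baseline, so one should be named in advance. In either case, reconcile the baseline-score-adjusted mixed model in the opening paragraph of Results with the GEE in the outcome sections, and state one covariate list (the primary-outcome list omits tenure).

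The change is one line of model specification. Four covariates at two follow-up visits add at least 4 × 2 = 8 interaction parameters, more if department/shift has several levels. In one simulated dataset the SE rose from 2.42 to 2.73: (2.73/2.42)² = 1.27, or 27% more variance, equivalent to about 39/1.27 ≈ 31 per arm. In another simulated setting it rose only from 2.70 to 2.74, about 3% more variance. Neither option removes unmeasured warehouse differences, because site and group are the same, and the report should say so.

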Self-prevention (PQ-derived domain mean; 7-point Likert scale; higher scores indicate better performance; scores are rescaled from 0 to 100) will be analyzed using GEE (identity link, Gaussian), clustering on participants with robust (sandwich) SEs and an exchangeable working correlation. The model includes group (ARPE vs. control), time (t_0_, t_1_, t_2_), group×time, site (fixed effect), and prespecified covariates (age, tenure, department/shift, prior training). Between-group change is tested via group×time with prespecified contrasts reporting marginal ARPE-control differences at t_1_ and t_2_ with 95% CI (two-sided α=0.05) and SMDs. Within-group change (t_1_-t_0_, t_2_-t_0_) will be presented using model-based marginal contrasts (descriptive). Missing data will be addressed under MCAR/MAR using GEE with robust SEs; sensitivity analyses will include inverse-probability-weighted GEE.

Secondary Outcome 2: Self-Evaluation 

Self-evaluation will be assessed using adapted RQ and SA domain means (7-point Likert scale; higher scores indicate better performance; scores are rescaled from 0 to 100). Repeated measures (t_0_, t_1_, t_2_) will be analyzed with GEE using an identity link and Gaussian family, clustering on participants with robust (sandwich) SEs and an exchangeable working correlation (Quasi-likelihood under the Independence model Criterion (for comparing GEE correlation structures) (QIC) to compare AR(1) and unstructured). The model includes group (ARPE vs. control), time, the interaction between group and time, site (fixed effect), and prespecified covariates (age, tenure, department/shift, and prior training). Between-group differences will be tested via the group×time interaction, with prespecified contrasts reporting marginal ARPE-control differences at t_1_ and t_2_ (95% CI; two-sided α=0.05; SMDs shown). Within-group changes (t_1_-t_0_, t_2_-t_0_) will be derived from model-based marginal contrasts (95% CI) and presented descriptively; inference will follow the GEE model.

Data Collection

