## Discussion

This protocol evaluates whether an AR-based physical ergonomics module (ARPE) improves ergonomic knowledge (primary) and self-prevention/self-evaluation (secondary) among MMH workers compared to guideline-based training. AR addresses the limitations of passive formats by increasing engagement, interactivity, and task-specific feedback, which are linked to better learning and skill transfer in professional training [26,27]. The quasi-experimental site/shift-level design aims to minimize cross-group contamination while allowing evaluation under routine working conditions [28]. Conventional classes and videos often fall short in changing behavior during high-risk tasks [7,11]. By incorporating 3D simulations and in situ cues, ARPE is expected to support deeper encoding, immediate feedback, and context-specific practice, potentially leading to safer work techniques. This study extends AR/VR training evidence to warehouse MMH ergonomics using validated tools, a prespecified analysis plan, and blinded assessment/analysis, which improves interpretability [26,27]. Strengths include alignment with occupational guidance and measures validated locally, pragmatic site/shift assignment to minimize contamination, repeated measures at T0, T1, and T2 to evaluate immediate gains and short-term durability, and a pre-planned model of group×time effects with covariate adjustment and site effects. Limitations persist. Additionally, we will perform inverse-probability-weighted sensitivity analyses. Self-report outcomes may be influenced by social desirability bias [29]; mitigation strategies include the use of anonymous, self-administered tools, blinded assessors and analysts, and aggregate reporting. Non-randomized allocation could lead to selection bias and site-level confounding [30]. We will report baseline comparability using SMDs, adjust for age, tenure, department/shift, and prior training, and include site effects. Contamination will be minimized through separate sites/shifts, instructions not to share materials, and routine schedule reminders. Expected attrition and varying digital literacy are addressed through weekly reminders, supervisor sign-offs, app usage analytics, and an intention-to-treat analysis with proper handling of missing data (MAR/MCAR). Residual confounding remains possible and will be considered in cautious interpretation.

Implications and future directions

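### The plan says unweighted GEE with robust SEs covers missing data under MAR; in general it does so only if the working correlation is correct

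*Protocol article*

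**What the plan says.** In the protocol article, Primary Outcome: Ergonomic Knowledge, the three assessments "will be analyzed using generalized estimating equations (GEE"). On incomplete data that section says: "Missing data will be managed under missing completely at random (MCAR)/missing at random (MAR) assumptions using GEE with robust SEs". Methods designed for MAR come second there, "with sensitivity analyses employing inverse-probability-weighted GEE and multiple imputation".

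The same rule appears under Secondary Outcome 1: Self-Prevention ("Missing data will be addressed under MCAR/MAR using GEE with robust SEs") and under Data Analysis ("Missing repeated measures will be addressed under MCAR/MAR assumptions via GEE with robust SEs"). The latter again places the alternatives second: "inverse-probability-weighted GEE and multiple imputation sensitivity analyses will also be reported". The model in Data Analysis is Gaussian with an identity link. On correlation and variance the text reads: "clustering on participants with robust (sandwich) SEs and an exchangeable working correlation; QIC will compare the exchangeable structure with AR(1)/unstructured structures". The Discussion describes the approach as intention-to-treat "with proper handling of missing data (MAR/MCAR").

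Three other statements bear on the point:

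- Sample Size plans for 40% attrition without dividing it between week 1 and week 6.
- The primary comparison is at week 1 (t1); week 6 (t2) is for durability.
- Planned outcomes and data analysis, and again Baseline Characteristics, say the repeated measures will be analysed with mixed models. This is not reconciled with the GEE text.

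**The concern.** GEE is not a likelihood method. With incomplete responses and no weights, its estimating equations are unbiased under MCAR, or when missingness depends only on covariates in the mean model. When dropout depends on earlier scores (MAR), the estimate is consistent only if the working correlation is also right. The sandwich estimator protects the variance against a wrong working correlation; it does nothing for the point estimate. So the text attributes to the primary method a property that it lacks in general.

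This is a stated rule, repeated in three sections, so it is not a detail left to an analysis plan. An exchangeable structure treats the week 0–1, 0–6 and 1–6 correlations as equal, which such uneven spacing makes doubtful. Dropout that acts differently by arm cannot be excluded. One warehouse uses a phone app and the other attends lectures, follow-up is by online form only, and the Discussion itself mentions varying digital literacy. Superiority is decided by whether a 95% CI excludes 0, so a shift in the estimate feeds directly into the conclusion.

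**Working it through.** **Attrition.** The plan's figure reproduces as 28 × 1.40 = 39.2, so 39 per group. A 40% loss from 39 is 15.6 missing and 23.4 remaining per group by the end. (Whether that inflation suffices is a separate matter.)

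**Where the bias comes from.** Take the case in which all loss occurs by week 1 and depends on baseline. Let δ be the shift in mean baseline score (SD units) of those who remain in an arm. Their mean score at visit k is shifted by ρ₀ₖδ. Exchangeable GEE with estimated correlation α removes αδ. The bias in the group×time contrast is therefore

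(ρ₀ₖ − α) × (δ_ARPE − δ_control).

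It vanishes if either factor is 0. Non-zero bias needs a correlation that is not exchangeable **and** dropout that differs by arm.

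**Simulation.** 200,000 per arm, Gaussian outcome, dropout depending on the last observed score. All correlations and dropout slopes are assumptions. Bias is in SD units; Monte Carlo error is about 0.005–0.01.

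| True correlation 0–1 / 0–6 / 1–6 | Dropout | Lost by t1 / t2 | Bias t1 | Bias t2 |
|---|---|---|---|---|
| 0.5 / 0.5 / 0.5 | opposite by arm | 20% / 40% | 0.010 | 0.019 |
| 0.6 / 0.36 / 0.6 | MCAR | 20% / 40% | −0.003 | 0.000 |
| 0.6 / 0.36 / 0.6 | same in both arms | 20% / 40% | −0.001 | −0.002 |
| 0.6 / 0.36 / 0.6 | one arm only | 40% / 40% | 0.033 | −0.051 |
| 0.6 / 0.36 / 0.6 | opposite by arm | 40% / 40% | 0.065 | −0.097 |
| 0.3 / 0.2 / 0.7 | same in both arms | 40% / 40% | −0.001 | 0.002 |
| 0.3 / 0.2 / 0.7 | one arm only | 40% / 40% | −0.033 | −0.066 |
| 0.3 / 0.2 / 0.7 | opposite by arm | 20% / 40% | −0.025 | 0.096 |
| 0.3 / 0.2 / 0.7 | opposite by arm | 40% / 40% | −0.074 | −0.140 |

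With the correct correlation structure the bias stayed within 0.01 throughout.

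**Hand check of the last row.** An independence working correlation (α = 0) gave 0.194 at t1, so δ_ARPE − δ_control = 0.194 / 0.3 = 0.647. With the estimated α = 0.40, the formula gives (0.3 − 0.40) × 0.647 = −0.065 at t1 and (0.2 − 0.40) × 0.647 = −0.129 at t2. The simulated values are −0.074 and −0.140.

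**Further runs.** A second simulation (300,000 per arm) gave up to 0.06 SD at t1 and 0.16 SD at t2 with opposite mechanisms. It gave about half that when only one arm's dropout was score-dependent, and about 0 when both arms were alike. With 5% lost by week 1, the t1 bias was about 0.01 SD. An unstructured working correlation left about 0.02 SD.

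**These are not bounds.** If the full 40% were lost by week 1 and the correlations were 0.7 / 0.4 / 0.5 (average 0.53), the formula with a similar δ difference gives about (0.7 − 0.53) × 0.65 = 0.11 SD at t1.

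**Scale.** With unit SD and baseline correlation 0.5, the contrast has SE √(4 × 0.5 / n). At n = 39 this is 0.226, and 0.07 / 0.226 = 0.31 SE. At n = 23 it is 0.295, and 0.16 / 0.295 = 0.54 SE.

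**Type I error** at 39 per arm (3,000 runs, z-test, t1/t2), under MAR:

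- 7.7% / 8.1% for correlations 0.7 / 0.4 / 0.5
- 6.0% / 6.9% for 0.4 / 0.3 / 0.7
- 5.8% / 6.5% for an exchangeable truth

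Under MCAR it was 5.1–6.6%. Part of the excess is thus ordinary small-sample behaviour of the sandwich estimator.

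**The case against.** Much of the case for leaving the plan alone is sound.

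- **The working correlation is not blindly fixed.** QIC will compare exchangeable with AR(1) and unstructured, and an unstructured Gaussian GEE removes most of the bias. In one rerun with SD 15, it left at most 0.2 points at t1 and 0.4 at t2, that is 0.2/15 = 0.013 and 0.4/15 = 0.027 SD. This stands, but no rule says the comparison changes the primary model, and QIC need not select unstructured.
- **A reader might infer that the primary result is likely to be biased.** The documents do not support that. Sample Size attributes attrition to turnover in shift work, and tenure and department/shift are model covariates. Nothing says that dropout follows scores or does so differently by arm.
- **A reader might apply the 40% to the primary time point.** The article does not divide it by visit, and at week 1 the loss may be small.
- **A reader might infer that no rule ranks the analyses.** One does: GEE is primary, and weighted GEE and multiple imputation are sensitivity analyses that will be reported. Nor are those the only MAR-oriented methods named, since mixed models appear too.
- **Larger threats exist.** With one warehouse per arm, site confounding outweighs a bias of this size. Small-sample corrections are commonly left to an analysis plan, so their absence is not the fault here.

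None of this makes the stated claim correct. It limits how much the error matters.

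**Conclusion.** The statement that unweighted GEE with robust standard errors handles MAR is wrong in general and should be corrected. The likely consequence is modest. Under assumed adverse mechanisms, the between-group bias in the simulated patterns reached about 0.06–0.07 SD at week 1, falling to about 0.01 SD with 5% lost by then, and 0.16 SD at week 6. It is about 0 if dropout acts alike in both arms, and at most about 0.02 SD if the true correlation is exchangeable.

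The week-6 durability contrast and the secondary outcomes at week 6 are therefore more exposed than the week-1 primary comparison. The sizes rest on assumed correlations, dropout slopes and timing of loss, none of which the article gives. The wrong claim itself and the unreconciled naming of both mixed models and GEE rest on the text alone.

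**What to change.** Resolve the conflict between the two named models. The preferred course is to make the likelihood-based mixed model already named under Planned outcomes and data analysis primary: REML, unstructured 3×3 covariance and small-sample degrees of freedom. GEE, weighted GEE and multiple imputation then become sensitivity analyses.

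If GEE is to remain primary, apply it after multiple imputation or with inverse-probability-of-missingness weights (distinct from the treatment weights mentioned elsewhere). At the least, fix an unstructured working correlation in advance and add a small-sample correction.

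Either way, delete the unqualified claim that unweighted GEE with robust standard errors covers MAR, in all three analysis sections and in the Discussion, and apply the same rule to the secondary outcomes.

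The cost is wording and slightly more modelling work, with the same data and software. An unstructured 3×3 covariance has 6 parameters against 2 for exchangeable, so 4 more are estimated from 78 participants. The article reports that follow-up continues and no interim results exist, so the change can still be prespecified if made before analysis.
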